#### Primary Outcomes

The feasibility of conducting a future RCT will be determined through the trial’s retention rate. The retention rate will be calculated by dividing the number of participants who completed all end point assessments (week 6) by the number of total randomized participants at baseline. As discussed, there are so far no other harm reduction–oriented studies in this population to guide our study design. Therefore, to establish an adequate minimum retention rate, we looked at related trials of (1) psychosocial mobile health interventions in populations with psychotic disorders, which had retention rates ranging from 76% to 100% [40-43] and (2) RCTs of face-to-face cannabis interventions for people with FEP, which had retention rates ranging from 52% to 96% [44-47]. The mobile health intervention trials either did not include comparison groups, did not focus specifically on individuals with FEP who used cannabis, or did not evaluate cannabis-focused interventions. The face-to-face interventions all focused on cannabis use in people with psychosis, but the delivery method precluded generalization to our trial. Given our intervention characteristics, we expect our retention rate will be on the lower end of these spectrums. We believe a 75% retention rate is a conservative estimate, but we are setting the minimum threshold for retention rate at 60%, which we believe represents a clinically important retention rate for our population.

Acceptability of the CHAMPS intervention will be assessed using the CHAMPS completion rate. This rate will be calculated by dividing the number of participants who completed at least the first 4 modules of CHAMPS by the number of total participants randomized to CHAMPS. We selected this completion threshold as the first 4 modules represent the core of the intervention, exposing participants to psychoeducation, motivational interviewing, personalized feedback, and skills training.

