### Study Aims

Our team developed a novel harm reduction intervention for individuals with FEP who are interested in reducing their cannabis use–related harms, called the Cannabis Harm–reducing Application to Manage Practices Safely (CHAMPS), which is delivered through a smartphone app. The development of CHAMPS was informed by related projects in cannabis use and psychosis conducted by our team [8,18,26] and co-designed in collaboration with clinicians, patient-partners, and experts in cannabis and psychosis (see intervention description in the Study Arms section). To our knowledge, the CHAMPS intervention represents the first psychosocial mobile health intervention aiming to reduce cannabis use–related harms in people with FEP. Our team is also currently working on a psychosocial mobile health intervention that addresses CUD in people with FEP and focuses on decreasing cannabis use or cessation [27].

Due to the paucity of cannabis harm reduction research in this population, a preliminary assessment of trial feasibility and intervention acceptability as well as an initial assessment of key clinical outcomes were necessary before conducting a large-scale randomized controlled trial (RCT) of CHAMPS [28]. As EIS represent the mainstay of treatment for FEP [29], we opted to evaluate this novel intervention as an adjunctive clinical tool to existing services. We will thus evaluate CHAMPS+EIS versus EIS-only in a multicenter, 2-arm, parallel group, open-label, randomized pilot study. The primary objectives of our study are to assess whether it is feasible to conduct a future RCT of the CHAMPS intervention in people with FEP who use cannabis and want to modify their cannabis behaviors and determine if CHAMPS is an acceptable intervention for this population. Secondary objectives aim to descriptively determine whether CHAMPS+EIS influences the use of protective behavioral strategies (PBS) and motivation to change PBS, compared to EIS only, in young people with psychosis who use cannabis. Exploratory objectives aim to descriptively estimate the effect of the intervention arm on cannabis-related problems, quality of life, cannabis and other substance use, severity of dependence, psychotic symptoms, and health care service use. We hypothesize that CHAMPS will be acceptable to those randomized to the CHAMPS+EIS intervention arm and that the pilot trial will demonstrate adequate feasibility, with a minimum trial retention rate of 60%.

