## Methods

### Participants and Recruitment

This study will involve 100 young adults (50 per arm) who meet the study’s eligibility criteria. Briefly, the inclusion criteria are having a diagnosis of psychosis, being 18 to 35 years old, having recent cannabis use, and being treated at an EIS (see Textbox 1 for detailed inclusion and exclusion criteria). Participants will continue their usual pharmacological and psychosocial interventions offered at the EIS, including taking any medication prescribed for their psychosis or other health concerns while participating in this study; these will be recorded in the patient study file.

If the CHAMPS intervention is considered clinically relevant for a potential participant, a clinician approaches this person, briefly explains the intervention, and asks about any interest in meeting the research team to learn more about the trial. If the person agrees, the referring psychiatrist or clinician collects screening and medical eligibility information. In other words, participant recruitment will use purposive sampling. The research staff then schedules a full screening visit, where eligibility is confirmed, and informed consent is obtained from interested participants (Figure 1; Multimedia Appendices 1 and 2). For study visits conducted via telepsychiatry, e-consent and verification of comprehension are documented using the Research Electronic Data Capture (REDCap; Vanderbilt University) web-based data entry system [30].

Clinicians will assist participants as needed, as they download the CHAMPS app from the Apple Store or the Google Play Store. If potential participants do not own a smartphone, the research staff will loan them a smartphone for the study duration. All participants will receive a compensation of CAD $30 (US $22.14) for participating at each visit (eg, screening, baseline, and follow-up assessment visits), with a maximum of CAD $150 (US $110.69) per participant. In addition, participants randomized to the EIS-only arm are offered CHAMPS access after their trial completion; these data will not be collected for research purposes.

Inclusion and exclusion criteria for participants and recruitment sites.

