### Sample Size

The sample size for pilot trials is typically not driven by power calculations but rather by convenience or precision estimates [62], both of which we used to inform our sample size. Using a precision-based approach, we estimated the number of participants we would need to retain in this trial to detect with 95% confidence the true retention rate for a future trial. As aforementioned, based on related literature and our current context, we deemed 60% a clinically significant retention rate for this trial [40-43]. As seen in Figure 4, if we recruit 100 participants and retain at least 69 participants at the end of the study, we would have 95% confidence that the true (ie, population-level) retention rate is above 60%. Regarding convenience, our existing partnerships with Canadian EIS clinics and experience recruiting relatively large samples from this population [63] lead us to believe that recruiting 100 eligible individuals is feasible for this trial.

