### Statistical Analysis

We will be analyzing primary outcomes using univariate analyses. The trial retention rate will be measured in terms of the percentage of randomized individuals retained in the intervention at end point assessment and will include a 1-sided 95% confidence interval to estimate the lower bound of the retention rate. CHAMPS acceptability will be reported using univariate analysis. We will also conduct exploratory analyses to test whether belonging to either study arm influenced EIS completion rates.

To describe sociodemographic and clinical variables at baseline, trial parameter data, and secondary and exploratory outcomes, we will conduct univariate analyses. We will use multivariable statistical methods to explore the following outcomes: participant satisfaction, use of cannabis PBS, and motivation to change cannabis PBS. To compare satisfaction between groups, we will use a hierarchical linear regression. The first regression model will insert the intervention arm as the independent study variable; the second model will insert other covariates. We will also conduct a hierarchical linear regression exploring the use of cannabis PBS over time as the outcome; the first regression model will insert study arms as the independent variable, and the second model will insert baseline PBS scores and other relevant covariates. To look at motivation to change, analyses will be done as with cannabis PBS, using hierarchical models that look at RCQ scores as the outcome and control for RCQ scores at baseline.

In multivariable models, we will include sites as random effects and will include certain covariates of interest that differ at baseline. These covariates may include age, sex, gender, study site, education status, employment, housing status, social support, and baseline clinical characteristics including cannabis use and CUD severity. Sensitivity analyses will explore key outcomes in subgroups of participants (eg, location-based subgroups), as well as the use of different thresholds to determine whether participants have completed CHAMPS.

Missing data will be handled issuing guidance of the missing data treatment for each instrument. The proposed analyses will include all participants with at least 1 nonmissing visit. Our analysis plan includes both intention-to-treat and per-protocol analyses.

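### The plan does not say whether the observed retention rate or its one-sided 95% lower bound must clear 60%, and for 60 to 68 of 100 retained the two readings disagree

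*Protocol article*

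**What the plan says.** Four sections of the protocol article bear on the feasibility criterion.

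- **Study Aims.** The hypothesis is that the pilot will show adequate feasibility, "with a minimum trial retention rate of 60" per cent.
- **Primary Outcomes.** "The feasibility of conducting a future RCT will be determined through the" trial's retention rate. That rate is an observed proportion: "The retention rate will be calculated by dividing the number of participants who completed all end point assessments (week 6"), over all randomized participants. The section then says "we are setting the minimum threshold for retention rate at 60" per cent. It gives 75% as a conservative expectation.
- **Sample Size.** The approach is based on precision. If 100 are recruited and the trial can "retain at least 69 participants at the end of the study", then "we would have 95% confidence that the true (ie, population-level) retention rate is above 60" per cent.
- **Statistical Analysis.** The retention analysis "will include a 1-sided 95% confidence interval to estimate the lower bound of the retention rate". The section does not say what the bound is compared with, or that it decides anything.

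**The concern.** The same 60% is attached to two different quantities. In Study Aims and Primary Outcomes it is a minimum for the rate the trial observes. In Sample Size it is a level the true rate should be shown to exceed. An observed 60% of 100 participants is far from showing that the true rate is above 60%.

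Retention is the stated determinant of whether a full-scale trial is feasible. If the observed rate decides, the 95% confidence used to justify 100 participants plays no part in the decision. If the lower bound decides, Study Aims and Primary Outcomes understate the bar. Unless the rule is fixed beforehand, a result of 60 to 68 retained could be called feasible or not feasible after the data are seen.

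**Working it through.** **Inputs.**
- n = 100. Participants and Recruitment: "This study will involve 100 young adults (50 per arm").
- Threshold 60% (Study Aims, Primary Outcomes, Sample Size).
- One-sided 95% confidence, so α = 0.05 (Statistical Analysis).
- Required count 69 (Sample Size).
- Expected retention 75% (Primary Outcomes).

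**Step 1: reproduce the plan's 69 of 100.** The exact (Clopper-Pearson) one-sided lower bound for x retained out of n is the 0.05 quantile of a Beta(x, n − x + 1) distribution.

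| Retained of 100 | Beta parameters | Exact lower bound |
|---|---|---|
| 60 | 60, 41 | 51.3% |
| 68 | 68, 33 | 59.5% |
| 69 | 69, 32 | 60.5% |

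The smallest count with a bound above 60% is 69, as the plan says. Equivalently, for X ~ Binomial(100, 0.60), P(X ≥ 69) = 0.0398, which is below 0.05, while P(X ≥ 68) = 0.0615, which is above it. The Wilson bound also gives 69 (59.9% at 68, 61.0% at 69).

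**Step 2: the two readings.**
- Observed-rate reading: feasible if x/100 ≥ 0.60, so x ≥ 60.
- Lower-bound reading: feasible if the exact bound exceeds 0.60, so x ≥ 69.

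They differ for x = 60 to 68, where the exact bound runs from 51.3% to 59.5%.

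**Step 3: how often each reading declares feasibility.** With X ~ Binomial(100, p), the three columns are P(X ≥ 60), P(X ≥ 69) and their difference.

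| True retention p | Observed rate ≥ 60% | Lower bound > 60% | Between: 60 to 68 retained |
|---|---|---|---|
| 55% | 18.3% | 0.3% | 18.0% |
| 60% | 54.3% | 4.0% | 50.3% |
| 65% | 87.5% | 23.3% | 64.2% |
| 70% | 98.8% | 63.3% | 35.4% |
| 75% (plan's expectation) | >99.9% | 93.1% | 6.9% |

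**Step 4: other numbers randomized.** The same exact calculation gives a minimum of 63 of 90 (bound 61.1%; 62 of 90 gives 59.9%) and 75 of 110 (bound 60.1%; 74 of 110 gives 59.2%). The cut therefore has to be recalculated if the final number is not 100.

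**The case against.** A reader might infer that the plan declares two conflicting success rules. The article does not support that. The only stated criterion is the 60% minimum. The 69 of 100 is a conditional precision statement used to justify the sample size, and nothing says that fewer than 69 means not feasible. The interval in Statistical Analysis is described as estimation. The sections can even be read as one rule: 60% is the floor for the true rate, and the lower bound is how it is checked. That reading is possible, but it requires taking retention rate in Primary Outcomes to mean the true rate, when the section defines it as an observed proportion. What remains is that the link between threshold and bound is not stated.

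A reader might also fault the plan for not naming the interval method. That is detail an article may leave to a fuller document, and the stated 69 already fits an exact or Wilson bound. A Wald bound would pass at 68 (60.3%), so the choice matters at one count only. It is not part of this point.

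Two further objections have weight. At the plan's own 75% the disputed range has a probability of only 6.9%. And this is a pilot that will report both the rate and its lower bound, so readers can apply either standard. Both limit the practical consequence, but neither tells the reader which quantity decides. Primary Outcomes itself expects retention towards the lower end of published ranges, one of which starts at 52%, and Limitations anticipates possible retention difficulties.

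**Conclusion.** The point holds as a gap between the stated feasibility threshold and the basis for the sample size. Followed literally, the 60% minimum on the observed rate does not deliver the 95% confidence for which 100 participants were chosen: 60 of 100 would pass with an exact lower bound of 51.3%. The consequence is large if true retention is between 60% and 70% (a 35% to 64% chance of landing in the disputed range at 60%, 65% and 70%) and small if it is near 75% (7%).

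These figures assume exactly 100 randomized, independent participants with a common retention probability, and an exact interval. They also assume that the 69 counts the same event as the primary outcome, namely week-6 assessment completion. Sample Size refers to the end of the study and Statistical Analysis to retention in the intervention, so that wording should be aligned as well.

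**What to change.** State one rule in Study Aims, Primary Outcomes and Statistical Analysis: feasibility is met when the exact one-sided 95% lower limit for week-6 retention among all randomized participants exceeds 60%. For 100 randomized this means 69 or more retained, which matches the plan's own figure. The count should be recalculated for the number actually randomized.

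The edit is short, but its effect is more than wording if the observed rate was meant to decide: the stated bar rises from 60% to 69% observed. No additional participants or data are needed. Because Results reports that enrollment has closed, the change should be dated and made without reference to the retention data.

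If the sponsor intends the observed rate to decide, the alternative is to keep the 60% minimum and say in Sample Size that meeting it does not give 95% confidence that the true rate is above 60%.

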#### Secondary Outcomes

The efficacy of CHAMPS will be described by examining the change in participants’ use of PBS, using the Short Form Protective Behavioral Strategies-Marijuana measure [21]. This is a 17-item self-report measure that includes evidence-based strategies that promote safer cannabis experiences. The marginal reliability of the short-form measure is high (0.93) [21].

The efficacy of CHAMPS will also be estimated by measuring the change in participants’ motivation to change PBS, which is assessed using the Readiness to Change Questionnaire (RCQ) modified for cannabis use [48,49]. The RCQ is a 12-item clinician-administered measure based on Prochaska and DiClemente stages-of-change model and assesses 3 stages of change: precontemplation, contemplation, and action [49]. The internal consistency is satisfactory; the 3 stages of change scales have acceptable internal consistency, ranging from Cronbach α=.73 to α=.85 [48].

#### Exploratory Outcomes

Cannabis use–related physical, psychological, social, and functioning problems will be assessed using the Marijuana Problems Scale, a 19-item self-report instrument that measures changes in problems related to cannabis use over time [50,51].

Cannabis and other drug use in the past 2 weeks will be assessed using the Timeline Follow-back. This tool has high test-retest reliability and has been validated using other measures of drug-related problems or in clinical populations [52,53]. This tool has previously been used in a trial of people with psychosis who use cannabis [54]. This tool assesses the self-reported days of cannabis use per week, as well as the type of cannabis products, quantity, and dose or concentration of cannabinoids. The main end point for this outcome will be the number of days per week of cannabis use. The frequency of other drug use in the past 2 weeks will also be assessed using this tool.

Psychotic symptoms will be measured using the Positive and Negative Syndrome Scale-6, which is easily administered and has good psychometric properties [55,56]. The scale consists of 6 items: delusions, conceptual disorganization, hallucinatory behavior, blunted affect, passive or apathetic social withdrawal and lack of spontaneity, and flow of conversation.

Severity of cannabis dependence will be measured using the Severity of Dependence Scale [57]. This is a short, easily self-administered instrument developed to provide a brief measure of the psychological aspects of dependence experienced by users of various types of illicit drugs. It is a measure of compulsive use. This scale has good internal consistency (Cronbach α ranging from .80 to .90) [57,58] and has previously been used in trials with people with FEP [5,59].

Health service use data are collected via participant self-report and are confirmed as needed through patient medical record abstraction and contact with the clinician, gathering information on the total number of past-month emergency visits and days of hospitalization.

### Data Collection and Management

Participation in the trial lasts up to 22 weeks, including up to 4 weeks between screening and randomization, 6 weeks of active CHAMPS intervention (immediate end point assessment), a booster session 4 weeks after the end of active CHAMPS intervention, and follow-up assessments conducted at weeks 12 and 18 (Table 2). Assessments are conducted either in person, over the phone, or using videoconferencing platforms. Communication and contact can be done digitally, over the telephone, or during in-person visits (only if confidentiality can be strictly maintained). All interactions are recorded in the patient study file. Furthermore, sites track participant interactions and collect information on recruitment, ineligibility reasons, and nonparticipation reasons. The research team uses these data to refine the recruitment strategy during the trial if needed.

**Table 2 table2:** Schedule of assessments.

Assessment name	Time point										
	Screening visit (week-4-2)	Baseline (W-2-W0)	Week 1	Week 2	Week 3	Week 4	Week 5	Week 6	Week 10	Week 12	Week 18
Screening form	✓										
Informed consent form	✓										
Locator form	✓							✓		✓	
Demographic questionnaire		✓									
Social Provision Scale-10		✓									
Readiness to Change Questionnaire		✓						✓		✓	✓
Marijuana Problems scale		✓						✓		✓	✓
Timeline Follow-back		✓						✓		✓	✓
Positive and Negative Syndrome Scale		✓						✓		✓	✓
Severity of Dependence Scale		✓						✓		✓	✓
Health care use		✓						✓		✓	✓
Randomization		✓									
Protective Behavioral Strategies—Marijuana		✓						✓		✓	✓
Client Satisfaction Questionnaire								✓		✓	
Adverse events								✓		✓	✓
Intervention and services form								✓		✓	✓

Data are entered into REDCap by site research staff or directly by the participant (through the CHAMPS app). The data dictionary will be built on REDCap and will be available upon request to the corresponding author. Final data quality assurance checks will be conducted by the data management team, and the study database will be locked, prohibiting further modification. The REDCap system was developed and implemented by the Center for Integration and Analysis of Medical Data to ensure that guidelines and regulations surrounding the use of computerized systems in clinical trials are upheld.

Participants are attributed a unique numeric study identifier to anonymize data, and data are password-protected on computerized databases and kept strictly confidential. Records are accessible only to research staff. Intervention arm participants are provided with detailed information regarding their data usage and protection (Multimedia Appendix 3). The final analysis data set will be kept on the secure server at the CHUM in Montreal, Québec, for 10 years, in line with *Fonds de la recherche en santé du Quebec* and CHUM research ethics board requirements.

An independent data and safety monitoring board examines accumulating data to ensure the protection of participants’ safety during the study. This board determines whether there is ground for trial continuation; evidence that study procedures require modifications; or whether the trial should be halted for participant safety, intervention efficacy issues, or inadequate trial performance reasons.

### Sample Size

The sample size for pilot trials is typically not driven by power calculations but rather by convenience or precision estimates [62], both of which we used to inform our sample size. Using a precision-based approach, we estimated the number of participants we would need to retain in this trial to detect with 95% confidence the true retention rate for a future trial. As aforementioned, based on related literature and our current context, we deemed 60% a clinically significant retention rate for this trial [40-43]. As seen in Figure 4, if we recruit 100 participants and retain at least 69 participants at the end of the study, we would have 95% confidence that the true (ie, population-level) retention rate is above 60%. Regarding convenience, our existing partnerships with Canadian EIS clinics and experience recruiting relatively large samples from this population [63] lead us to believe that recruiting 100 eligible individuals is feasible for this trial.

